### Phase 1: web-based survey

Phase 1 will address objectives 1 and 2. Responses will be collected from BCNs via a web-based survey to investigate the following feasibility domains [34]:Acceptability: e.g. How helpful are formal assessment tools to assess patients for FoR?Demand: e.g. What is the estimated proportion of patients who experience moderate and high levels of FoR, and how is it currently managed in practice?Practicality: e.g. What support do BCNs currently receive to fulfil their role and help patients deal with psychological issues? What barriers do they encounter using assessment tools in clinical practice?Adaptation: e.g. Do BCNs receiving training to deal specifically with FoR?Integration: e.g. Would BCNs be interested in taking part in a training course for Mini-AFTER and what would this consist of?

The web-based survey will be conducted via the Bristol Online Survey tool [35], which is fully compliant with all UK data protection laws and is highly accessible across different organisations.

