### Phase 1 sampling and recruitment

The survey link and participant information sheet will be sent via email to members enrolled on Breast Cancer Care’s Nursing Network database (*n* = 905). Breast Cancer Care is a UK-based breast cancer charity. This organisation hosts a database of 905 health professionals working directly with people affected by breast cancer, of which 65% are BCNs. A prerequisite of joining the network is that a health professional must spend at least 50% of their time working with people affected by breast cancer. This number is consistent with data published by Macmillan Cancer Support [36–39]. With no other national register of BCNs in the UK, this route is the most direct way for the research team to access the study population. However, further steps will be taken to increase awareness among BCNs across the UK about the study through hospital networks and regional BCN groups to enhance our overall recruitment.

Eligibility criteria (being a BCN) will be detailed in the email, participant information sheet and consent page. Six weeks after the initial email, a reminder will appear in an email bulletin, circulated by Breast Cancer Care. The survey will be open for a period of 12 weeks.

Demographic data will be gathered about the age of participants, number of years working with people affected with breast cancer, number of years qualified, job banding, clinical area they align with, i.e. surgery, oncology, medical, highest level of clinical attainment, number of BCNs in the respondents’ workplace, numbers of newly diagnosed patients with breast cancer in their hospital and respondents’ place of work.

Table 3 illustrates the flow of the topics through the survey and examples of questions from each topic section. The questions were developed by the team and guided by the NPT approach illustrated in Table 2. The survey will be piloted among the research team, nurses working on the helpline at Breast Cancer Care (*n* = 4) and BCNs working in the NHS (*n* = 2) to test access and responses before it is distributed. In order to reduce bias, these nurses will be excluded from completing the survey and future studies.

**Table 3 Tab3:** Survey structure and example questions

Section	Example questions	Question type
1. Consent	• Do you consent to taking part in this survey?	• Multiple choice^a^

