2. About you	• No. of years working with people affected by breast cancer? • How many breast care nurses work on your team? • Approx. what proportion of your role is spent in the following areas?	• Multiple choice • Multiple choice • Scale^b^
3. About the patients you meet with breast cancer	• What psychological care interventions do you provide to patients with breast cancer?	• Multiple choice
	*FoR definition provided*	
	• In your opinion, what proportion of your patients experience FoR at a moderate level? At a severe level?	• Multiple choice
4. About the work you do	• Approx. what proportion of patients do you discuss FoR with? • How is the issue of FoR generally raised? (I always raise a discussion on FoR vs. I only discuss FoR if the patient raises it) • In your experience, what factors trigger FoR in a breast cancer patient? • What barriers do you encounter using assessment tools in clinical practice?	• Multiple choice • Scale • Freetext^c^ • Freetext
4. About the support within your team	• What kind of formal support do you receive to fulfil your role? • How would you rate the support you get from your team when helping patients deal with psychological issues? (Extremely supportive vs. Not at all supportive) • How would you rate the formal support you receive to fulfil your role?	• Multiple answer^d^ • Scale • Scale
5. About your preferred support	• Have you received training to deal specifically with the area of FoR?	• Multiple choice
	*Brief explanation of the Mini-AFTER intervention provided*	
	• If you were offered a one-day training course to implement the Mini-AFTER intervention, would you accept it?	• Multiple choice
6. About other support services you use	• If you identify a patient with moderate FoR, which of the following services do you refer them to? With severe FoR? • How do you decide which service to refer your patient to when they have FoR?	• Multiple answer • Freetext
7. Follow-up	*Explanation of Phase 2 of the study provided*	
	• Would you be willing to take part in a telephone interview? • Would you be interested in delivering the Mini-AFTER intervention in a future study?	• Multiple choice • Multiple choice

^a^Multiple choice questions allow respondents to pick just one answer from a list of pre-defined answers

^b^Scale questions ask respondents whether they agree or disagree with a number of statements, to rate items on a scale, or to rank items in order of importance

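### Table 3 asks nurses where they refer moderate and severe FoR only after Mini-AFTER has been explained, so those current-practice answers may be primed

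*Protocol article*

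**What the plan says.** Under the heading Phase 1: web-based survey, the article states that "Phase 1 will address objectives 1 and 2". Objective 1 concerns how breast care nurses identify and manage FoR at present. The Demand domain under the same heading puts it as "What is the estimated proportion of patients who experience moderate and high levels of FoR, and how is it currently managed in practice".

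The section on Phase 1 sampling and recruitment introduces the questionnaire with "Table 3 illustrates the flow of the topics through the survey and examples of questions from each topic section". In that table, section 5 (preferred support) contains the entry "Brief explanation of the Mini-AFTER intervention provided", followed directly by "If you were offered a one-day training course to implement the Mini-AFTER intervention, would you accept it". Section 6 (other support services) comes next, with a multiple-answer item, "If you identify a patient with moderate FoR, which of the following services do you refer them to? With severe FoR", and a free-text item, "How do you decide which service to refer your patient to when they have FoR". Section 7 closes with willingness to be interviewed and interest in delivering Mini-AFTER.

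**The concern.** A description of usual practice is best taken before respondents are told about the intervention that might change it. Here the nurse first reads about Mini-AFTER. The Background says it was developed for moderate FoR and is a single structured call made by a breast care nurse. The nurse then says whether to accept training, and only after that reports where moderate and severe cases are sent and how that is decided. The description and the answer just given could colour the report.

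The referral items are the listed items closest to usual care for the group Mini-AFTER is meant for. Phase 1 results shape the Phase 2 interview questions, and the combined findings feed the decision on whether and how to develop a larger trial. Evidence on current handling of moderate FoR should therefore be as free of prompting as the questionnaire can make it.

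**Working it through.** No arithmetic applies. The check is of order and content.

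1. **Is the printed order the survey order?** The text says "Table 3 illustrates the flow of the topics through the survey", so the sections can be read as a sequence. No other part of the article gives a different order.

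2. **What comes before the explanation?** The table prints the number 4 twice; both sections precede section 5.
   - Section 3: psychological interventions provided; a definition of FoR; the share of patients thought to have moderate and severe FoR.
   - Section 4 (work): the share of patients with whom FoR is discussed; how it is raised; triggers; barriers to assessment tools.
   - Section 4 (team support): formal and team support.
   - Section 5, first item: whether FoR-specific training has been received.

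3. **What comes after it?**
   - Section 5, remainder: the training offer.
   - Section 6: referral for moderate FoR, referral for severe FoR, and how the service is chosen.
   - Section 7: interview and delivery interest.

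4. **Which of the later items describe current practice?** Only those in section 6. The training offer and the section 7 items ask about future willingness and properly follow the explanation.

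5. **Do other listed items cover the same ground?** Section 3 separates moderate from severe, but asks how common each is, not what is done about it. Sections 3 and 4 ask about interventions and discussion without splitting by level. Among the listed items, section 6 alone asks about management by level.

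6. **Is there a stated reason or safeguard?** The article gives no reason for the order and mentions no locked pages. The pilot is meant to check access and responses. If all testers see one order, as the table implies, it could not reveal an order effect. The Limitations section deals with response and access only.

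The order is therefore as described, and it affects two listed questions, one of which has a moderate and a severe part.

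**The case against.** The case for leaving the order alone has several parts.

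- **The moderate/severe split is already there.** Section 3 introduces it, and the referral item carries it in its own wording. This stands: a reader might infer that the explanation creates a sharper distinction between levels, but the questionnaire supplies that distinction whatever the order.
- **The referral item is a tick-list of services.** It asks for a largely factual report, which probably leaves less room for reframing. This also stands, and it is why the free-text item is the more exposed of the two.
- **No named analysis depends on the order.** A reader might infer that associations between current management and training acceptance are inflated because the answers sit next to each other. The document does not support this. The one item-level association it names links how FoR is raised (section 4) with interest in delivery (section 7). The Data analysis section otherwise refers to training level, experience and service environment. No named analysis pairs section 6 with the training offer.
- **The stakes are modest.** The survey is largely descriptive, no numerical progression rule rests on section 6, and the interviews return to current practice. This lowers the weight of the point. It does not remove it, because interviewees receive an information pack on Mini-AFTER beforehand, so the interviews cannot supply an unprompted account either.
- **Re-ordering may not give a clean baseline.** The information sheet goes out with the survey link and its content is not shown. This stands as a limit on the remedy. Moving section 6 would still remove the explanation and the training question from immediately before the referral items.

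**Conclusion.** The point holds as a minor fault of questionnaire order. The listed items on referral of moderate and severe FoR, which serve objective 1, follow the Mini-AFTER explanation and the training offer, and nothing elsewhere in the article corrects this. All respondents who follow the printed order are affected.

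The size and direction of any effect cannot be obtained from the document. A nurse might present a tidier referral pathway, or might stress a gap that Mini-AFTER would fill; these point in different ways, and neither can be assumed.

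A reader might also infer that the whole current-practice baseline is compromised. It is not: the listed items in sections 3 and 4 precede the explanation, referral is only one part of management, and the exposure is to a brief description rather than to the intervention itself.

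The conclusion assumes that the live survey follows Table 3 and that the explanation conveys Mini-AFTER's purpose, as any fair summary would. Because the table lists examples only, nothing can be said about items it does not show.

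**What to change.** Before launch, move section 6 ahead of the Mini-AFTER explanation in section 5, so that all listed current-practice items are answered first. Keep the training offer and the delivery-interest item after the explanation. If the survey tool allows it, prevent return to earlier pages once the explanation has been shown; the article does not say whether it does, and the main change does not depend on it.

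This adds no items, respondents or time. It would also help to check how much the information sheet says about Mini-AFTER, since re-ordering cannot undo exposure before the first question. If the present order is kept, state it as a limitation when the referral results are reported, particularly for the free-text item.

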### Phase 2: qualitative interviews

Phase 2 will address objectives 3 and 4 but will also be grounded in the quantitative results from the first phase, allowing us to explore and elaborate further on areas of importance to the overall study.

### Phase 2 sampling and recruitment

The final survey question will invite participants to take part in a 40-min telephone interview. Depending on the number of participants agreeing to be interviewed, and following analysis of the data from phase 1, a purposive sampling matrix will be developed. If numbers allow, two demographic factors such as age, number of years qualified, years in current post or level of educational attainment will be combined with sub-groups based on the answers to the following two key questions which may predict willingness to use the Mini-AFTER intervention:How is the issue of FoR generally raised? (I always raise a discussion vs. I only discuss FoR if the patient raises it)How comfortable are you discussing FoR with your patients? (Extremely comfortable vs. Not at all comfortable)

To achieve the planned matrix and reach data saturation, an overall sample size of 20 will be required.

Prior to interview, an information pack about the Mini-AFTER intervention will be sent to each selected participant. This pack will be made up of a participant information sheet re-iterating the eligibility criteria, an online presentation and extracts from the Mini-AFTER manual. Interviews will be digitally audio recorded and conducted over the phone by ES.

Interviews will explore BCNs’ views on the importance of addressing FoR in their clinical consultations, and how the Mini-AFTER intervention could be successfully integrated in practice. Phase 2 will also provide valuable information regarding the design and perceived feasibility of a future RCT, including the following domains [40]:Eligibility—who (people affected by breast cancer) will participate in the trial?Recruitment—how will participants be recruited into the trial?Setting—where will the trial be conducted?Organisation—what training and resources will be needed to deliver Mini-AFTER?Delivery—how should Mini-AFTER be delivered?

Table 2 illustrates how the interviews questions will be guided by NPT and provides examples of questions for each NPT component.

### Validity of interview data

To ensure a consistent interview style is used with all interview participants, ES will be the sole interviewer. Direct anonymised quotations will be used to illustrate findings in any future publications, presentations or reports. Double coding and utilisation of NVivo’s coding comparison query [41] on 25% of the transcripts will ensure consistency and rigour across the whole of the data.

### Data analysis

The survey data will be collected, coded and entered into SPSS 22 [42]. Descriptive statistics will be used to summarise the sample characteristics and responses to questions. Multiple responses from the same centre will be controlled for using a clustering approach.

Descriptive analysis of cross-sectional data will be reported to understand how FoR is currently identified and addressed in breast cancer patients. Associations will be examined to investigate variation in these responses according to self-reported training level, experience and service environment. Barriers to formal assessment and systematic intervention of FoR in clinical practice will be investigated.

We will use conventional random intercept/slope regression models with continuous and binary-dependent variables using suitable procedures in STATA (xtmixed and xtmelogit). We will perform tests using these approaches to determine if a multi-level approach is required. That is, the two procedures xtmixed2 (for continuous response data) and xtmelogit2 (for categorical data response data) will provide a likelihood-ratio statistic to indicate if variance within clusters (i.e. the BCNs from the same cancer units) is significant. To estimate these multi-level models the ‘marginal likelihood’ has to be estimated using approximate methods [43]. This approach uses an adaptive quadrature procedure which enables efficient solutions to be obtained and reduced computation time. A sensitivity analysis will be performed to determine the appropriate number of integration points to obtain the most precise estimation.

Audio recordings from interviews will be transcribed verbatim, and all identifiable information will be removed from the transcripts. Framework analysis will guide the analysis of the qualitative data via a five-step process: (1) familiarisation with the data; (2) identifying a thematic framework based on emerging themes or issues in the data; (3) indexing the data in relation to specific themes; (4) charting the data based on the indexed themes; and (5) mapping and interpretation of the data to analyse the key characteristics in the charts (35). All members of the research team will be involved in at least one step in the process to ensure both researchers and lay representatives contribute their expertise at all stages of the study. However, ES, DF, SC and JA will be involved in all steps.

Coding of the data will be informed by the four main components of NPT (coherence, cognitive participation, collective action and reflexive monitoring, Table 2), but will also provide enough flexibility for any new themes that may emerge. Double coding will be employed on 25% of the transcripts to ensure any bias in the interpretation of the data is highlighted. Qualitative data will be coded and managed using NVivo 10 software [41].

Following analysis of the two sets of data, the research team will integrate the results to reflect the outcomes of the entire study. Firstly, the quantitative results will be interpreted to answer objectives 1 and 2. Secondly, the qualitative findings will enable the phase 1 data to be further clarified by explaining the statistical results and addressing detail for objectives 3 and 4. The final stage will be to discuss and group the findings from both sets of data to the NPT framework and feasibility domains to ensure the decision about how, or indeed, whether a larger trial of the Mini-AFTER intervention could be developed, ultimately leading to its implementation in practice, is achieved.

## Discussion

The prevalence of FoR and the major impact it has on breast cancer survivors’ quality of life, psychological state and use of healthcare services leads to the need for interventions to be developed to support breast cancer patients with both severe and moderate levels of FoR. There are a number of interventions being designed and tested [14, 15, 44, 45]; however, there is no routinely available intervention in practice to help support people with moderate FoR following treatment for cancer. Indeed there is evidence that some health professionals are not managing the issue of FoR even when it is brought to their attention [1]. This has the potential to harm breast cancer survivors as well as contribute to an increased use of healthcare services in an attempt to seek ways to cope with their fear [7, 46]. Delivery of a nurse-led telephone intervention to address FoR could not only relieve some of the pressure on healthcare services for follow-up cancer care, but also better serve the psychological needs of breast cancer survivors.

This study has been designed to provide an overview (Phase 1) as well as an in-depth insight (Phase 2) into how FoR is currently being managed in practice, and what factors will contribute to the successful implementation of the Mini-AFTER telephone intervention. Use of NPT will inform specific aspects of the implementation of this intervention, such as whether it would promote or impede BCNs’ work, what impact it would have on their resources and how it would fit with the overall goals of their organisation/wider policy agenda. Findings will also provide information to inform the development of an RCT to test the effectiveness of the Mini-AFTER intervention.

### Limitations

The study may be limited by low response rates. We are relying on BCNs opening their email from Breast Cancer Care and reading the contents. With the function of automatic sifting of email, we may find that some BCNs are not contacted through this route. The use of reminders may mitigate against this. Another limitation is that we are accessing BCNs through a single route rather than directly through their organisations. Although the Breast Cancer Care Nursing Network is the most comprehensive database of BCNs working in the UK, and the most comprehensive route to accessing BCNs across the country, the research team will raise awareness of the work among BCN through hospital and regional BCN networks.

## Abbreviations

BCN: Breast care nurse
FoR: Fear of recurrence
RCT: Randomised control trial
